# Effects of aquatic exercise program versus on-land exercise program on cancer-related fatigue, neuropathy, activity and participation, quality of life, and return to work for cancer patients: study protocol for a randomized controlled trial

**DOI:** 10.1186/s12906-024-04367-8

**Published:** 2024-02-02

**Keywords:** Aquatic therapy, Cancer, Participation and activity, Quality of life, Return to work

## Abstract

**Background:**

Exercise has shown positive effects on fatigue, exhaustion, neuropathy, and quality of life in cancer patients. While on-land exercises have been studied, the aquatic environment offers unique advantages. Water's density and viscosity provide resistance, enhancing muscle strength, while hydrostatic pressure improves venous return. This trial aims to investigate the effect of aquatic exercises on time to return to work, work hours, work-related difficulties, daily life activity and participation, quality of life, exhaustion, fatigue, and neuropathy among cancer patients, compared to on-land exercise intervention group and a non-exercise group.

**Methods:**

This randomized controlled trial will include 150 cancer patients aged 18–65 years with stage III colon cancer or breast cancer patients with lymph node involvement. Participants in the aquatic exercise intervention group will undergo an 8-week, twice-weekly group-based Ai-Chi program, while the on-land exercise group will perform identical exercise. The control group will not engage in any exercise.

The primary outcome will be assessed using an employment barriers questionnaire, capturing return to work date and working hours and daily life participation and activity and quality of life. Secondary outcomes include exhaustion, fatigue, and neuropathy. Data will be collected at baseline, post-intervention (8 weeks), and at 3,12, and 24 months. Mixed variance analyses will explore relationships among groups and over time for independent variables, with separate analyses for each dependent variable.

**Discussion:**

The potential benefits include an earlier return to work for patients, reducing their need for social and economic support. The study's implications on socio-economic policies are noteworthy, as a successful intervention could offer a cost-effective and non-invasive solution, improving patients' quality of life and increasing their participation in daily activities. This, in turn, could lead to a faster return to work, contributing to both personal well-being and broader societal interests by reducing reliance on social services.

**Trial registration:**

The trial is registered at ClinicalTrials.gov NCT05427344 (22 June 2022).

**Supplementary Information:**

The online version contains supplementary material available at 10.1186/s12906-024-04367-8.

## Introduction

### Background and rationale {6a}

The number of patients being treated for cancer continues to grow [1], which presents a challenge to treatment centers, health and welfare systems, and to the patients themselves. The majority of cancer patients experience exhaustion and fatigue [2, 3], as well as neuropathy [4, 5], as a consequence of their treatments. These factors adversely impact their participation in daily activities and reduce their quality of life [6, 7]. Additionally, they may affect the ability to function at work and delay a return to employment [8, 9].

Clinical studies have demonstrated that physical activity has a positive effect on the levels of exhaustion and fatigue [10], as well as neuropathy [11], and the general quality of life [12] of cancer patients. Consequently, patients being treated for cancer are advised to avoid inactivity [10, 13]. Paradoxically, this may lead to a scenario where exhaustion and fatigue contribute to decreased physical activity, while decreased physical activity increases exhaustion and fatigue [14], and may even be associated with a decreased quality of life among cancer patients [15, 16]. Therefore, it is important to determine the type of exercise that is most beneficial for patients and encourages them to persevere.

Most previous studies have focused on the effect of exercise on land [17]. For example, various literature reviews [18] have described the practice of Tai Chi as beneficial in reducing exhaustion and fatigue to some extent, and have suggested that it may improve the quality of life of cancer patients. The environment in which physical activity takes place is important. In this context, the properties of water and their effect on the submerged human body may be particularly beneficial for cancer patients. The density and viscosity of the water provide muscle resistance and thus improve muscle strength, while the hydrostatic pressure improves venous return, and immersion in water permits motility that is not possible on land [19]. Previous studies among breast cancer patients reported that exercise in water reduced fatigue [20, 21]. However, there is not much evidence for this topic. It is possible that the combination of the advantages of an aqueous environment and those of Tai Chi may be beneficial to cancer patients, and this represents the focus of the present study. The practice of Tai Chi in water was developed by Jun Konno and is termed Ai Chi [22]. Participants in Ai Chi perform 19 movements based on the Tai Chi Chuan technique while immersed in water to shoulder height [23].

### Objectives {7}

Based on the literature review described above, the objectives of the present study are:

(A) To examine the effects of an 8-week physical activity program in water, on time to return to work, work hours, perception of work-related difficulties, and work absenteeism, among cancer patients, as compared to an intervention group undergoing identical physical exercise on land, and a third group with no additional exercise.(B) To examine the effects of an 8-week physical activity program in water on activity and participation in the daily life and quality of life of cancer patients compared with the other two intervention groups (the same physical activity on land and the group without further physical exercise).(C) To examine the effects of an eight-week water exercise program on exhaustion, fatigue, and neuropathy in cancer patients compared with the other two intervention groups (the same physical exercise on land and the group without further physical exercise).

### Trial design {8}

This is the protocol of a parallel-group, controlled, randomized trial, with a pre-post and repeated follow-up measures between-group design.

A three-arm trial is going to be carried out. Participants who meet the recruitment criteria bellow will be randomly assigned to Group 1: Water exercise group, Group 2: Land exercise group, or Group 3: Control group. The assessment will be conducted at five-time points: an initial assessment before being randomized (pretreatment; T0), at the end of the intervention (post-treatment; T1), 3 months after the completion of the intervention (T2), 12 months after the completion of the intervention (T3), and 24 months after the completion of the intervention (T4). CONSORT patient’s flowchart is presented in Fig. 1.

**Fig. 1 Fig1:**
[figure not shown]
CONSORT flow diagram

## Methods: Participants, interventions and outcomes

### Study setting {9}

The trial will take place at Tel Aviv University and the Hadassah Medical Center hydrotherapy pool, Israel.

### Eligibility criteria {10}

Criteria for inclusion in the study will be: (a) age between 18–65; (b) diagnosis of cancer; and (c) a score above 26 on the cognitive MOCA test [24]. Volunteers with orthopedic injuries that in the opinion of the attending physician prevent their participation in physical exercise, or individuals engaged in other physical activity on a regular basis, will not be eligible to participate in the present study. Recruitment of colorectal cancer patients and breast cancer patients for the study will be within 3 months of cessation of chemotherapy treatment.

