### Primary outcome

Employment Barriers Questionnaire [25] and Date of return to work and duration of working hours—self-report by the study participants.WHODAS 2.0—to examine the degree of activity and participation in daily life [26].EORTC QLQ-C30—to evaluate the quality of life from the point of view of the participant [27].

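### Return to work is the first objective and a primary outcome, but neither the entry rules nor the analysis limit it to participants who had a job and were off work at baseline

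*Protocol article*

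**What the plan says.** Objectives {7} lists as the first aim the effect of the water programme "on time to return to work, work hours, perception of work-related difficulties, and work absenteeism, among cancer patients". Under Primary outcome, the Employment Barriers Questionnaire is joined by "Date of return to work and duration of working hours—self-report by the study participants", alongside WHODAS 2.0 and EORTC QLQ-C30.

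Eligibility criteria {10} begins "Criteria for inclusion in the study will be: (a) age between 18–65; (b) diagnosis of cancer" and adds a MOCA score above 26. It excludes disabling orthopaedic injury and "or individuals engaged in other physical activity on a regular basis, will not be eligible to participate in the present study". Recruitment "will be within 3 months of cessation of chemotherapy treatment" is the only timing rule. The abstract and Sample size {14} add tumour type and stage. None of these places refers to a job before diagnosis or to being off work at T0.

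Statistical methods {20a} plans mixed variance analyses, one for each primary and secondary outcome, and names no analysis set for any of them. Section {20c} says missing data will be imputed by random forest, with no outcome exempted. Section {20b} plans no additional analyses. Randomisation {16a} is simple, and Sample size {14} rests on WHODAS 2.0 alone.

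**The concern.** A date of return to work is defined only for someone who had work and was away from it. The stated criteria also admit three other kinds of participant: those with no job before diagnosis, those who worked through chemotherapy or went back before T0, and those near the upper age limit who may retire during follow-up (8 weeks plus 24 months, about 26 months). The first have nothing to return to. The second have a date that precedes randomisation, which the programme cannot have changed.

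The plan as written does something with these people. Either they receive a fixed score, which is the same in every arm and pulls the contrast towards zero, or their missing date is filled in by the imputation model, which invents an event. A null result on objective A could then reflect who was enrolled and not what the programme does. Earlier return to work is also the main societal benefit claimed in the Discussion.

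**Working it through.** **The plan's own figure.** Sample size {14} uses a difference of 15, SD 15.08, alpha 0.05 (two-sided assumed) and 80% power: n = 2 × (1.960 + 0.842)² × (15.08/15)² = 15.9, so 16 per group. This reproduces, and 50 per group were chosen. The calculation concerns WHODAS 2.0, so the article states no power for return to work.

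**Inputs for the illustration.** From the article: 50 per arm. Assumed, because the article gives none of them: return proportions of 40% and 70% among those at risk, an at-risk share f of 80%, 60% or 50%, and a two-sided 5% test of two arms.

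**Formula.** Power = Φ[(|p₂ − p₁| − 1.96 × SE₀) / SE₁], with SE₀ = √[2p̄(1 − p̄)/n], p̄ = (p₁ + p₂)/2, and SE₁ = √{[p₁(1 − p₁) + p₂(1 − p₂)]/n}.

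- Everyone at risk: p₁ = 0.40, p₂ = 0.70, n = 50. SE₀ = 0.0995, SE₁ = 0.0949, and (0.30 − 0.195)/0.0949 = 1.11, so power is 87%.
- Rest counted as not returned: p₁ = 0.40f, p₂ = 0.70f, n = 50.
- Rest counted as already returned: p₁ = 1 − f + 0.40f, p₂ = 1 − f + 0.70f, n = 50.
- At-risk set only: p₁ = 0.40, p₂ = 0.70, n = 50f.

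| At-risk share f | Difference if all are counted (0.30f) | Power, rest not returned | Power, rest already returned | Power, at-risk set only (n per arm) |
|---|---|---|---|---|
| 100% | 30 points | 87% | 87% | 87% (50) |
| 80% | 24 points | 68% | 71% | 78% (40) |
| 60% | 18 points | 48% | 53% | 65% (30) |
| 50% | 15 points | 39% | 43% | 57% (25) |

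**Sensitivity to the rates.** With 50% versus 75% in place of 40% versus 70%, power is 74% if all are at risk. At f = 80% and 60% it is 52% and 34% with the rest counted as not returned, and 64% and 52% in the at-risk set. The pattern is the same.

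The test of proportions is a simple stand-in for the planned analysis. It shows the direction of the effect and how it scales, and does not predict this trial's power.

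**The case against.** The strongest reply is that section {20a} never says all participants enter every analysis, that someone with no job simply has no return date, and that analysis sets are commonly left to a statistical analysis plan, which is not shown. It is true that the article does not name the set, so dilution is not a stated intention. The reply does not dispose of the point. Eligibility belongs to the protocol, and the stated imputation rule exempts no outcome, so a blank return date for a participant with no job falls under it as written. A later plan can define the right set cleanly only if work status was recorded before randomisation. Some of that may already be captured, since working hours and the Employment Barriers Questionnaire are collected at baseline and the schedule figure is not visible here. Employment before diagnosis is not mentioned.

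Broad entry is also defensible. WHODAS 2.0 and QLQ-C30 apply to everyone, and WHODAS 2.0 sets the sample size. For that reason the remedy need not narrow recruitment.

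Two stronger readings are tempting. A reader might infer that many participants will be unable to have the event. The article gives no employment share, so that is possible but undocumented. A reader might also infer that such participants can contribute nothing to objective A. That is wrong: people already at work can contribute to work hours, perceived difficulties and absenteeism, and someone without a job at entry could start one during follow-up. The difficulty is specific to the return date.

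Chance imbalance in work status under simple randomisation is random variation and adds no bias to the argument.

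**Conclusion.** The point holds for the date of, or time to, return to work. A primary outcome is defined only for a subset that the plan neither recruits nor identifies, while its common analysis and blanket imputation would give values to people outside that subset. If any such participants enrol and are given a fixed result, the contrast shrinks in proportion to the at-risk share. That direction does not depend on whether they are coded as never or already returned.

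The size cannot be derived from the article. The fall from 87% to between 68% and 39% rests entirely on assumed return rates and at-risk shares. Restricting to the at-risk set recovers part of the loss (78% to 57%) but stays below 80% in each of these scenarios, so the gain is mainly in interpretability. WHODAS 2.0, QLQ-C30, fatigue and neuropathy are unaffected.

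**What to change.** 1. At T0, before randomisation, record employment before diagnosis, current work status and hours, usual hours before diagnosis, and any retirement planned within follow-up.
2. Define the return-to-work population as participants employed before diagnosis and off work at T0. Include those on reduced hours, with return defined for them as resuming their pre-diagnosis hours.
3. Exempt the return date from imputation for anyone outside that population.
4. Analyse work hours, work-related difficulties and absenteeism in all participants employed before diagnosis, including those already back at work, adjusting for the T0 value.
5. Keep all 150 for WHODAS 2.0, QLQ-C30, fatigue and neuropathy.
6. State in Objectives {7} and under Primary outcome which population answers each part of objective A, and report the size of the return-to-work population by arm.

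The cost is a few baseline questions and a short amendment, with no extra patients or visits. Recruitment began in April 2023 and is due to end in August 2027, so later entrants can be captured prospectively. For those already enrolled, pre-randomisation work status has to be obtained retrospectively, and since participants know their allocation this should be flagged as recalled information. The main downside is that the return-to-work result will rest on fewer than 50 per arm if anyone falls outside the population. It is not covered by the WHODAS-based sample size, and the report should say so.

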### Who will take informed consent? {26a}

At the initial screening, participants will receive informed consent from their doctor and will have the opportunity to ask questions about their participation. After that, they will receive the informed consent form and will ask to sign it.

### Additional consent provisions for collection and use of participant data and biological specimens {26b}

In this study, biological samples will not be collected. Participant data will be used only for the research proposes.

### Interventions

#### Explanation for the choice of comparators {6b}

The land exercise group is chosen in order to control for the environmental aspects of the intervention and the control group was chosen in order to control for the motor aspect of the intervention.

### Intervention description {11a}

(A) Water exercise group where the Ai-Chi technique was selected as the exercise method of choice. The activity will take place in a hydrotherapy pool approved by the Ministry of Health and will be led by a hydrotherapist who has been trained in Ai-Chi.(B) Land exercise group who will perform the same Ai-Chi movements on land in order to standardize the groups. The activity will take place in a hall and will be led by a physiotherapist who has been trained to teach Ai-Chi on land.(C) Control group who will not perform additional physical activity or receive any extra treatments. In accordance with the recommendations for physical activity among cancer patients and the guidance of the hydrotherapy organization for hot water activities, the exercise program will be scheduled for 30 min twice a week for 8 weeks. The physical activities will take place in groups of 5 participants per group.

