### Sample size {14}

One hundred and fifty cancer patients aged 18–65 years (stage III colon cancer patients and breast cancer patients with lymph node involvement) will be recruited via advertisements in Hadassah Medical Center and Tal Aviv University. The sample size is based on data from the WHO Disability Assessment Schedule (WHODAS 2.0), which has been used internationally to assess function and disability among a healthy population versus an unhealthy population [26]. The expected difference in the questionnaire scores between the two groups is 15 points and the average standard deviation is 15.08. The sample calculation includes a type 1 error of alpha equal to 0.05 with a power of 80%. According to this calculation, 16 participants are needed in each of the three study groups. Because we anticipate the withdrawal of some of the participants and because of the clinical condition of all participants, a number of 50 participants per group was selected.

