### Statistical methods

#### Statistical methods for primary and secondary outcomes {20a}

Every participant will be assigned a random study identifier number, ensuring the privacy of their personal data. The statistical analyses will be conducted in a way that prevents the identification of individual patients. We will conduct a series of mixed variance analyses to identify relationships and associations between groups, as well as changes over time within each group (independent variables). The dependent variables will be primary and secondary outcomes, and a separate analysis will be performed for each variable.

Additionally, we will conduct various analyses to explore the relationships between changes in the dependent variables.

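### Both exercise arms are taught in classes of five but the stated model has no class term, so if classmates' outcomes are positively correlated the exercise contrasts get standard errors that are too small

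*Protocol article*

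**What the plan says.** Delivery is set out in the protocol article under Intervention description {11a}. Both exercise programmes run for 30 minutes twice a week for 8 weeks, and "The physical activities will take place in groups of 5 participants per group". The water programme "will be led by a hydrotherapist who has been trained in Ai-Chi" and the land programme "will be led by a physiotherapist who has been trained to teach Ai-Chi on land"; the number of instructors is not given. The third arm is different in kind: "Control group who will not perform additional physical activity or receive any extra treatments". Sequence generation {16a} describes simple randomisation of individual participants, approximately 1:1:1.

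The analysis is in Statistical methods {20a}: "We will conduct a series of mixed variance analyses to identify relationships and associations between groups", together with "changes over time within each group (independent variables". One analysis is run per outcome. Group and time are the factors named; class is not.

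Sample size {14} is a plain two-group comparison of WHODAS 2.0 means: "The expected difference in the questionnaire scores between the two groups is 15 points and the average standard deviation is 15.08". Error rate and power are also given: "The sample calculation includes a type 1 error of alpha equal to 0.05 with a power of 80" percent. The result, 16 per group, is raised to 50 for withdrawals and clinical condition. No ICC or design effect appears.

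**The concern.** This is an individually randomised trial with partial nesting: two arms are grouped after randomisation and one is not. The word mixed in a mixed analysis of variance covers repeated visits within a participant. It does not cover correlation between different participants who train together.

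Classmates share 16 sessions (2 per week for 8 weeks) and whatever support the class generates. The primary outcomes are self-reported work status, participation and quality of life, in participants who know their allocation, so some positive correlation within classes is plausible. If it exists and is ignored, confidence intervals are too narrow and p-values too small. Water versus land is the most exposed contrast because both of its arms are grouped, and Explanation for the choice of comparators {6b} relies on the land arm to control for the effect of the environment.

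**Working it through.** **Inputs from the protocol article.** Class size m = 5; 50 per arm, so 50/5 = 10 classes per exercise arm if classes are full and closed; difference 15, SD 15.08, alpha 0.05, power 80%. **Assumed:** the class-level ICC, which the article does not give, taken over 0.01 to 0.20 with zero as reference. The formulas apply to a comparison of two arm means at a post-baseline visit.

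**Step 1, the plan's own figure.** n = 2 × [15.08 × (1.960 + 0.842)/15]² = 15.87, rounded up to 16 per group. This reproduces the stated 16 (two-sided, normal approximation), with participants taken as independent.

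**Step 2, variance inflation.**
- Design effect: DE = 1 + (m − 1) × ICC = 1 + 4 × ICC.
- Water versus land: both arms are inflated, so the variance is multiplied by DE.
- Exercise versus control: only one arm is inflated, so the variance is multiplied by (1 + DE)/2.

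**Step 3, true size of an unadjusted 5% test.** With V the variance multiplier, size = 2 × [1 − Φ(1.960/√V)]. At ICC 0.05, DE = 1.20. For water versus land, 1.960/√1.20 = 1.789, giving 7.4%. For exercise versus control, V = 1.10 and 1.960/√1.10 = 1.869, giving 6.2%.

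**Step 4, required n per arm** = 15.87 × V, rounded up.

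| ICC (assumed) | DE | SE understated, water vs land | SE understated, exercise vs control | Size, water vs land | Size, exercise vs control | n needed, water vs land | n needed, exercise vs control |
|---|---|---|---|---|---|---|---|
| 0 | 1.00 | 0% | 0% | 5.0% | 5.0% | 16 | 16 |
| 0.01 | 1.04 | 1.9% | 1.0% | 5.5% | 5.2% | 17 | 17 |
| 0.05 | 1.20 | 8.7% | 4.7% | 7.4% | 6.2% | 20 | 18 |
| 0.10 | 1.40 | 15.5% | 8.7% | 9.8% | 7.4% | 23 | 20 |
| 0.20 | 1.80 | 25.5% | 15.5% | 14.4% | 9.8% | 29 | 23 |

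SE understated is 1 − 1/√V.

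**Step 5, power at the chosen 50 per arm.** For water versus land and 15 points, power = Φ{15/[15.08 × √(2/50) × √DE] − 1.960}. This is 0.999 with no clustering, 0.995 at ICC 0.05, 0.988 at 0.10 and 0.960 at 0.20. At ICC 0.20 the standardised difference is 15/(15.08 × 0.2 × 1.342) = 3.71. Testing it against a t distribution on 20 − 2 = 18 class-level degrees of freedom lowers power only to about 0.94.

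**The case against.** The strongest reply is that the article is a summary. A random class effect belongs to the error structure, would not normally be listed among independent variables, and could stand in an analysis plan that is not shown. The article nowhere says that participants are treated as independent; that is inferred from the factors it names. This stands as a caution. But the article does describe its model and its sample-size calculation, neither accommodates the delivery structure it also describes, and class membership has to be captured during conduct whatever a later plan says.

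Several stronger readings are tempting, and the document does not support them.

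- *That the standard errors are certainly too small.* This needs a positive ICC, for which the document has no figure. At 0.01 the effect is trivial. The ICC may also differ between outcomes and fade at the visits 3, 12 and 24 months after classes end.
- *That the trial is underpowered.* It is not for the planned 15-point difference, as steps 4 and 5 show.
- *That a shared instructor drives the correlation.* The number of instructors is not stated. If one person leads every class in an arm, instructor adds no variation between classes and is confounded with arm.
- *That classes running at different calendar times invalidate the comparison.* Individual randomisation balances calendar period across all three arms in expectation, so this mechanism is weak.

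It is also true that the article does not say whether classes are closed or rolling. Under Criteria for discontinuing or modifying allocated interventions {11b}, missing two or more sessions is a ground for discontinuation. Realised classes may therefore be smaller than five, with a smaller design effect.

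**Conclusion.** The point holds conditionally. The stated model does not match the stated delivery, and any positive correlation within classes makes the unadjusted test too liberal for contrasts involving an exercise arm. Over the assumed ICC range of 0.01 to 0.20, the inflation is from slight to nearly threefold for water versus land, and at most about twofold for exercise versus control. These figures rest on full, stable classes of five and on one ICC for all outcomes and visits.

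The harm is to error rates and interval width, not to the planned power. The larger sample does not cure it: the design effect depends on class size, so adding more classes of five leaves the inflation unchanged. The correction is worth making, but the size of the problem in this trial cannot be known from the document.

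**What to change.** - Record class membership for every water and land participant, with the dates attended, so that class can be defined even if entry is rolling. Recruitment is expected to run to August 2027, so this should start now.
- Add to the repeated-measures mixed model a random class effect in the two exercise arms only, with controls as singletons, and use small-sample degrees of freedom such as Kenward-Roger or Satterthwaite. Baseline is taken before randomisation, so the class effect should act on the post-baseline visits. A class intercept that also applies at baseline would cancel from the group-by-time contrast and leave its standard error uncorrected.
- Report the estimated ICC with its uncertainty.

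Arm-specific residual variances and a restated power calculation are optional.

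The cost is one recorded variable, one model term and slightly wider confidence intervals. With about 10 classes per arm the class variance will be estimated imprecisely. If one instructor leads all classes in an arm, the instructor effect stays confounded with arm. A class term cannot separate them, and the report should say so.
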